### Strategies to improve adherence to interventions

2.7

Standardized patient education with clear instructional materials and simplified dosing schedules will be explained in detail to patients or legal representatives. Regular monitoring of adherence through clinic visits and patient-reported diaries; proactive management of treatment-related adverse events to minimize discomfort; and supportive engagement with caregivers will be carried out to reinforce consistent administration. The investigators will maintain regular, empathetic communication to build trust and encourage sustained compliance.

### Discontinuation of the study protocol

2.8

The study maybe terminated for individual patients if the patient or their legal representative withdraws consent. Additionally, the investigator may terminate a patient’s participation at any time during the study if the patient meets any of the following termination criteria:*Hepatic function*: AST/ALT levels are ≥ 3 times the upper limit of normal (ULN), bilirubin levels are ≥ 2 times the ULN (with direct bilirubin accounting for at least 35% of the total), or the INR is > 1.5 (note that INR values do not apply to patients taking anticoagulants).*Cardiac safety*: Investigational medicinal products (IMPs) must be discontinued in patients who meet one of the following ECG criteria on the basis of the average of three readings: QTcF >500 ms, uncorrected QT > 600 ms, or QTcF change from baseline > 60 ms.*Infection*: The patient developed suspected new latent tuberculosis infection (LTBI), active tuberculosis (TB), or nontuberculous mycobacterial (NTM) infection during the study (including but not limited to confirmed conversion by interferon gamma release assay [IGRA] or other diagnostic methods).*Adverse reactions*: Significant unexpected adverse reactions, unexpected reactions of high severity, or other important safety results as determined by the Independent Data Monitoring Committee (IDMC).The trial site may also terminate or suspend the trial early if serious violations of good clinical practice (GCPs), the study protocol, or contractual agreements are identified, or if the site is unable to ensure sufficient enrollment of subjects.

The DSMB will regularly review the progress of the study and conduct interim assessments of safety data. They will provide recommendations to the sponsor regarding whether the nature, frequency, and severity of adverse reactions related to the study treatment warrant early termination or modification of the study to maximize patient benefit. If necessary, the sponsor may decide to terminate the trial.

### Withdrawal and replacement of individual subjects

2.9

Patients can leave the study at any time for any reason if they wish to do so without any consequences. The attending physician can decide to withdraw a subject from the study for medical reasons. After withdrawal, these patients will receive the standard ICU care.

### Outcome measures

2.10

The primary objective of the RADIA study was to determine whether treatment with BCDT followed by daratumumab would yield a more effective and rapid treatment response than standard immunotherapy, as measured by changes in mRS. The mRS is a well-established tool for assessing the degree of dependence and disability in daily activities (26); a decrease in the mRS score indicates increased independence and autonomy. Only patients with an mRS score ≥ 3 were included in the RADIA study, as this score indicates severe disability, where the patient is unable to walk independently and requires assistance with activities of daily living. The primary endpoint of the study was the proportion of patients who achieved an mRS score of ≤ 2 at 16 weeks following treatment initiation.

The secondary objectives of the study were to analyse the effects of daratumumab on disease severity at various time points throughout the study, as well as its impact on clinical assessment scales (e.g., Clinical Assessment Scale for Autoimmune Encephalitis (CASE) scores, MoCA, MMSE, NPI and laboratory parameters (e.g., blood immunoglobulin, lymphocyte subsets, memory B cells, and plasma cell subsets). Specifically, the secondary endpoints will evaluate the effects of daratumumab on the following:mRS score at 6, 16, 24, and 48 weeks following the first dose of the drug.CASE scores at 6, 16, 24, and 48 weeks following the first dose of the drug.Duration of ICU if patients are staying in ICU at treatment initiation.Cognitive function assessments (MoCA, MMSE, and NPI) will be performed at baseline and at each scheduled study visit, including infusion visits, with the primary analysis conducted at Week 16.Absolute and relative changes in serum autoantibody are measured at baseline and 16 weeks after the first dose of the study drug. To ensure methodological consistency across centers, all antibody testing will be conducted by a third-party central laboratory (KingMed Diagnostics, Guangzhou, China) using standardized commercial cell-based assays (CBA). Antibody positivity and titer interpretation will be determined according to the diagnostic cut-off values and procedures recommended by the assay manufacturers and established clinical protocols for autoimmune encephalitis. Specifically, serum and CSF antibody titers are determined by serial twofold dilutions. Positivity is defined as a serum titer ≥ 1:10 or a CSF titer ≥ 1:1, with a clear cell-surface fluorescence intensity of ≥ 2 + (on a 0–4 + scale) compared to the negative control, in accordance with the manufacturer’s instructions. Borderline results (e.g., titer = 1:10 with 1 + intensity) will be retested in duplicate; persistently borderline results will be reported as indeterminate.Immune status, including lymphocyte subsets, memory B cells, and plasma cell subsets.Safety parameters, including serious adverse events, were monitored within 16 weeks after the first dose of the study drug.

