### Sample size calculation

2.11

The sample size was calculated based on the primary endpoint, defined as the proportion of patients achieving a modified Rankin Scale (mRS) score ≤ 2 at 16 weeks after treatment initiation. Due to the absence of robust published data from randomized controlled trials in this specific patient population, the initial response rate assumptions were derived from limited retrospective studies and clinical experience in patients with severe autoimmune encephalitis.

Under the primary assumption of a 90% response rate in the BCDT followed by daratumumab group and a 70% response rate in the BCDT alone group, with a two-sided significance level of 0.05 (*α* = 0.05) and 80% power (*β* = 0.20), the estimated required sample size was 64 patients per group. After accounting for a 10% dropout rate, approximately 80 participants were estimated for each of the two active comparison groups. For the third group (repeated IVIG/PE), given the anticipated difficulty in recruitment and its role as an exploratory reference arm, the sample size was set at 40 patients. Thus, the total planned sample size was 200 patients.

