#### Definition of the primary efficacy endpoint and event definitions

2.12.1

The primary efficacy endpoint is the proportion of patients with an mRS score ≤ 2, assessed at 16 weeks after treatment initiation.

Relapse event: Defined as the occurrence of new or worsening neurological or psychiatric symptoms attributable to NMDARE following an initial period of at least 2 months of clinical improvement or stabilization, accompanied by at least one of the following: (1) recurrence or an increase in anti-NMDAR antibodies in cerebrospinal fluid (CSF) or serum; (2) new or worsening abnormalities on brain MRI consistent with encephalitis; or (3) new or increased epileptiform activity on EEG. All relapse events must be reviewed and confirmed by an independent adjudication committee (6, 21, 27, 28).

Rescue treatment event: Defined as the initiation of any additional immunotherapy beyond the assigned study treatment due to insufficient clinical improvement, clinical deterioration, or life-threatening complications. This includes, but is not limited to, cyclophosphamide, bortezomib, tocilizumab. The decision to initiate salvage therapy is made by the treating physician and subsequently reviewed and confirmed by the independent adjudication committee (21, 29).

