#### Analysis methods for primary and secondary endpoints

2.12.2

For the primary endpoint, the comparison of the proportion of patients achieving mRS ≤ 2 at week 16 between treatment groups will be performed using a Cochran–Mantel–Haenszel test stratified by study center, with a two-sided significance level of 0.05. A logistic regression model adjusting for stratification factors and baseline covariates (e.g., age, baseline mRS) will be used as a supportive analysis.

For time-to-event endpoints, including relapse and salvage treatment events, Kaplan–Meier curves will be used to summarize event times, and event rates with 25%/75% quartiles will be calculated. The stratified log-rank test will be used for intergroup comparisons, and hazard ratios with 95% confidence intervals will be estimated using a Cox proportional hazards model, with stratification factors included as covariates.

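### The primary objective, the sample size and the primary test do not name the same contrast, so the objective could be met on a comparison that cannot isolate daratumumab

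*Protocol article*

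**What the plan says.** Four places in the protocol article bear on which comparison decides the trial.

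- **Section 2.10 (primary objective).** The objective is "to determine whether treatment with BCDT followed by daratumumab would yield a more effective and rapid treatment response than standard immunotherapy", measured by change in mRS. The same section then fixes the endpoint as the proportion with mRS ≤ 2 at week 16, and Section 2.12.1 repeats it: "The primary efficacy endpoint is the proportion of patients with an mRS score ≤ 2, assessed at 16 weeks after treatment initiation".
- **Section 2.11 (sample size).** The assumption is "90% response rate in the BCDT followed by daratumumab group and a 70% response rate in the BCDT alone group", at two-sided 0.05 and 80% power. These two arms are treated as the active comparison. The IVIG/PE arm is set at 40 patients because of expected recruitment difficulty and "its role as an exploratory reference arm".
- **Section 2.12.2 (primary test).** A Cochran–Mantel–Haenszel test stratified by center, at two-sided 0.05, is applied to "the comparison of the proportion of patients achieving mRS ≤ 2 at week 16 between treatment groups". No pair of arms is named.
- **Section 1 (Introduction, last sentence).** The aim is the efficacy of daratumumab added to ofatumumab, which agrees with Section 2.11.

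**The concern.** With three arms, the plan has to say which difference carries the primary claim. The objective points to standard immunotherapy, the sample size points to BCDT alone, and the test points to no pair. The Introduction lists IVIG and plasma exchange as first-line and B-cell depletion as second-line, so the natural reading of the objective leads to the arm that Section 2.11 calls exploratory.

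Attribution is at stake. The combination and IVIG/PE arms differ by ofatumumab and daratumumab together, so a difference between them may come wholly from ofatumumab. A significant three-arm test may likewise reflect only the gap between BCDT and IVIG/PE. Section 1 cites a cohort in which BCDT improved outcomes over first-line therapy alone, so a gap of that kind is one the authors have reason to expect. Either result could be reported as meeting the stated objective although daratumumab added nothing.

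A smaller mismatch sits in the same sentence. The objective promises a more rapid response, but a single proportion at week 16 does not measure speed.

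**Working it through.** **1. Which contrast was sized?** Inputs from Section 2.11: p1 = 0.90 (combination), p2 = 0.70 (BCDT alone), two-sided α = 0.05, power 0.80. With p̄ = 0.80, the pooled-variance formula is

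n = [z(0.975)·√(2p̄(1−p̄)) + z(0.80)·√(p1(1−p1) + p2(1−p2))]² / (p1−p2)²

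= [1.960·√0.32 + 0.842·√0.30]² / 0.04 = 61.6, so 62 per group.

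The plan states 64, which is within two patients. The powered contrast is therefore combination versus BCDT alone.

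**2. The places side by side.**

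| Place | Comparator of the combination |
|---|---|
| Section 1, aim | ofatumumab without daratumumab |
| Section 2.10, primary objective | standard immunotherapy, no arm named |
| Section 2.11, sample size | BCDT alone; IVIG/PE exploratory |
| Section 2.12.2, primary test | not named |

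**3. What happens if daratumumab adds nothing?** Both BCDT arms are set at the plan's 70%. The IVIG/PE rate is an assumption, because the document gives none; 60%, 50% and 40% are shown. Arm sizes are 80/80/40 from the 2:2:1 allocation. Center strata are ignored.

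Normal approximation for combination versus IVIG/PE at 70% v 50%:

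- pooled rate = (56 + 20)/120 = 0.633
- null SE = √(0.633·0.367·(1/80 + 1/40)) = 0.0933
- alternative SE = √(0.21/80 + 0.25/40) = 0.0942
- probability of significance = Φ((0.20 − 1.96·0.0933)/0.0942) = Φ(0.18) = 57.2%

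The pairwise figures in the second column below come from exact enumeration of the unstratified chi-square test. The other two columns are simulated.

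| Assumed IVIG/PE rate | Combination v IVIG/PE | Three-arm test (2 df) | Combination v BCDT alone |
|---|---|---|---|
| 60% | 19.9% | 18% | 5% |
| 50% | 57.5% | 56% | 5% |
| 40% | 89.0% | 89% | 5% |

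The first two result columns depend almost entirely on how far IVIG/PE falls below BCDT. Only the last column responds to daratumumab itself, and it stays at its nominal level.

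**4. Error rate if several pairs were all confirmatory.** With all three arms at 70% and each pair tested at 0.05, at least one of three pairs is significant in about 12% of simulated trials. At least one of the two pairs involving daratumumab is significant in about 9%.

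**5. Does fixing the contrast cost patients?** The 80 per arm less 10% dropout gives 80·0.90 = 72. Exact unstratified power at 90% v 70% is about 87% at 72 per arm and 90% at 80 (normal approximation: 85.9% and 89.3%). Both exceed the stated 80%, so no patients are added.

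**The case against.** The strongest reply is that the intended contrast can already be found. Section 2.11 sizes the trial on the primary endpoint for combination versus BCDT alone and makes IVIG/PE exploratory, and the Introduction states the add-on aim. Standard immunotherapy might also be meant to include BCDT: the Summary puts good outcomes at about 70% under first-line therapy with or without second-line agents, the same figure that Section 2.11 assumes for BCDT alone. Naming the pair and handling multiplicity are often left to the SAP, which is not shown. Combination versus IVIG/PE is also a legitimate evaluation of the whole regimen, which Section 2.1 describes as the object of study. Finally, mRS at week 6 is a secondary endpoint, so early response is not ignored.

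Much of this stands. The mapping to IVIG/PE is the natural reading, not a stated one. Silence on multiplicity in Section 2.12.2 is not a fault by itself. The 12% and 9% figures describe a plan that the protocol does not set out.

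The reply does not remove the conflict. The primary objective and the powered contrast are both protocol content, both are printed, and they do not use the same comparator. If standard immunotherapy was meant to include BCDT, the objective is still ambiguous between two arms, and the test does not resolve it. An SAP that names BCDT alone would still leave the published objective to be corrected. One that names IVIG/PE would contradict Section 2.11.

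**Conclusion.** The point holds as an inconsistency in what the trial sets out to show. The objective names a comparator tied to no arm, the sample size and the aim rest on BCDT alone, and the test names no pair. As written, the objective could be met by a comparison that cannot isolate daratumumab. With no daratumumab effect, that would happen in about 20% to 89% of trials for combination versus IVIG/PE, over assumed IVIG/PE rates of 60% down to 40%. This rests on 70% in both BCDT arms, 80 v 40 patients and no center strata. The closer IVIG/PE lies to BCDT, the smaller the problem.

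A reader might infer more than the document supports:

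- *That the objective definitely names the IVIG/PE arm.* No section says so.
- *That the trial's type I error is 12%.* This would need all three pairs to be confirmatory at 0.05, and Section 2.11 points the other way.
- *That combination versus IVIG/PE says nothing about daratumumab.* It evaluates the two drugs together; it cannot separate them.
- *That the IVIG/PE comparison is underpowered against the stated 80%.* The plan gives no IVIG/PE rate and promises no power for that pair.

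**What to change.** 1. In Section 2.10, restate the primary objective as BCDT followed by daratumumab versus BCDT alone on the week-16 proportion with mRS ≤ 2.
2. In Section 2.12.2, name that pair as the sole primary contrast, tested at two-sided 0.05.
3. Report both contrasts with IVIG/PE as exploratory estimates with confidence intervals, or test them only after the primary contrast succeeds.
4. Delete the reference to rapid response from the primary objective, because the week-16 proportion does not measure speed. The mRS at week 6 remains as a secondary endpoint.

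The cost is wording in the protocol, with the SAP brought into line. No patients are added (step 5 of the working). The downside is that there is no confirmatory claim against IVIG/PE unless the primary contrast succeeds. The trial is open-label and has been randomizing since January 2025 (Section 2.1), so the change should be dated and made before any comparison of outcomes by arm. Otherwise the choice of contrast could look data-driven.

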### Trial design and setting

2.1

RADIA is a randomized, controlled, open-label, multicenter clinical trial initiated by investigators to assess the safety and efficacy of B-cell depleting therapy followed by daratumumab in patients with severe AE, with NMDARE as the primary target population. The study will be conducted in the Department of Neurology in 58 tertiary hospitals nationwide, with a planned enrollment of 200 patients by December 2026.

The study was approved firstly by the Institutional Review Board of the Third Affiliated Hospital of Soochow University. The first patient was randomized in Jan 2025. The participants will be randomly assigned to receive one of three treatment arms: B-cell-depleting agents (ofatumumab followed by daratumumab, B-cell-depleting agents (ofatumumab alone), or repeated IVIG/PE therapy. The flowchart outlining the recruitment, intervention, and evaluation processes is presented in Figure 1.

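### The serum antibody endpoint names absolute change of a twofold-dilution titre as one of its two measures; change in dilution steps (log2 titre) would serve better at no cost

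*Protocol article*

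**What the plan says.** Section 2.10 lists the antibody endpoint among the secondary endpoints: "Absolute and relative changes in serum autoantibody are measured at baseline and 16 weeks after the first dose of the study drug". The same item states that "serum and CSF antibody titers are determined by serial twofold dilutions" and sets the cut-off: "Positivity is defined as a serum titer ≥ 1:10 or a CSF titer ≥ 1:1". Borderline samples are retested, and those that stay borderline are reported as indeterminate.

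Section 2.12.2 names methods for the primary endpoint (Cochran-Mantel-Haenszel test, logistic regression) and for time-to-event endpoints (Kaplan-Meier, log-rank, Cox). It names no test, model or transformation for titre change.

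The third arm receives "or repeated IVIG/PE therapy". Section 2.11 describes that arm as an exploratory reference and sizes only the two active arms, at 80 patients each with 10% dropout.

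**The concern.** The measure and the assay do not fit each other. A twofold series is geometric, so one step is the same biological and assay unit anywhere on it. Subtracting raw reciprocal titres gives that one step a weight proportional to the starting titre. A comparison of mean absolute change then reflects mainly the few patients who start highest, and a real shift across the arm can be missed.

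The Summary section gives reduction of pathogenic antibody as one of the things the trial investigates, and the Introduction rests the case for daratumumab on antibody-secreting cells. A false null on serum titre would therefore weaken the biological argument. The article also lists absolute and relative change side by side without ranking them, so the two could disagree with no rule for which one counts.

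**Working it through.** **The plan's own figures.** No power or sample size is stated for the antibody endpoint, so there is none to reproduce. The number of patients comes from section 2.11. For the primary endpoint ("90% response rate in the BCDT followed by daratumumab group", "70% response rate in the BCDT alone group", "with a two-sided significance level of 0.05", 80% power) the usual formula gives

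n = (1.96 × √(2 × 0.8 × 0.2) + 0.8416 × √(0.9 × 0.1 + 0.7 × 0.3))² / 0.2² = (1.109 + 0.461)² / 0.04 ≈ 62,

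close to the stated 64. With 80 per active arm and 10% dropout, 80 × 0.9 = 72 per arm have week-16 data. That is the number used below.

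**Scale, by arithmetic alone.** Let B be the baseline titre (reciprocal) and Δ the change in log2 steps.
- Absolute change = B × (2^Δ − 1). For Δ = −1 this is −160 from B = 320 and −10 from B = 20.
- Relative change = 2^Δ − 1, which is −50% in both cases. B cancels.

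So absolute change carries the whole baseline spread and relative change does not. If the baseline SD is 2 steps (assumed), a patient one SD above the mean has 2⁴ = 16 times the titre of a patient one SD below. The same one-step fall counts 16 times as much, and 16² = 256 times as much in squared terms.

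Relative change increases with Δ. A rank test on it is therefore identical to a rank test on log2 change. A t-test loses something, because relative change cannot go below −100% but has no upper bound.

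**Size, by simulation.** The article gives no titre distribution, variability or expected effect, so these are assumptions. Titres are 10 × 2^k, rounded to whole steps, with negatives one step below 1:10; two-sided α is 0.05.

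Setting A: 72 per arm, true difference one step, change SD 1.7 steps, baseline SD 1 to 2.5 steps.

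| Measure | t-test | Rank test |
|---|---|---|
| Absolute change | 8-37% | 28-43% |
| Relative change | 62-74% | 76-93% |
| Log2 titre, ANCOVA on baseline | 85-94% | not run |

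A repeat with mean baseline 3, 4 or 6 steps above 1:10 and a two-step mean fall in the control arm agreed with these ranges to within about two percentage points.

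Setting B: 72 per arm, mean baseline 6 steps, baseline SD 1 to 2.5, change SD 1 to 2, difference chosen for about 80% power on log2 change.

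| Measure | t-test | Rank test |
|---|---|---|
| Absolute change | 5-28% | 10-37% |
| Relative change | 44-66% | 72-79% |
| Log2 change | 74-80% | 72-79% |

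Both settings give the same order. The loss on absolute change is large and ranks do not repair it. The loss on relative change is moderate with a t-test and absent against the log2 rank test when ranks are used.

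**The case against.** The strongest reply is that the article defines a measure and states no analysis. Log transformation, ranks or ANCOVA are not excluded, absolute change could even be meant in dilution steps, and the model for a secondary laboratory endpoint normally sits in an analysis plan, which is not shown here. This stands in part: the missing test is no fault, and the text cannot be said to commit the trial to a t-test on raw titres. What remains is that the article itself names the change scales, absolute first, and an analysis plan that follows it inherits them.

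Three stronger readings are tempting and are not supported.
- A reader might infer that most of the power of the whole endpoint is lost. That is true only of the absolute measure; relative change keeps more than half of the log2 power in every setting run.
- A reader might infer that both scales are driven by the highest titres. Relative change divides each patient by their own baseline, so it is not.
- A reader might infer that plasma exchange, which removes serum antibody directly, spoils the endpoint. Section 2.11 already gives that arm a reference role, and Table 1 schedules IVIG/PE at weeks 4, 8 and 12 rather than at the week-16 sample. The documents do not show the size of any remaining effect.

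Nor is serum titre the only mechanistic readout: section 2.10 lists plasma cell subsets separately.

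**Conclusion.** The concern holds for absolute change. On a twofold-dilution titre it is a poorly suited scale, and under the assumed spreads it has roughly 8-37% power by t-test (28-43% by ranks), against about 85-94% for baseline-adjusted log2 titre. Relative change is acceptable if ranked and moderately inefficient if t-tested.

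The mismatch of scale follows from the article's own definitions. The power figures rest on spreads and a one-step effect that the article does not give. No test is stated in the article, and the primary endpoint and the sample size are unaffected. This is a free improvement, not a defect that threatens the trial.

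**What to change.** In section 2.10 (and in the analysis plan), define the endpoint as the change in log2 serum titre, that is the number of dilution steps, from baseline to week 16. Compare ofatumumab followed by daratumumab with ofatumumab alone by ANCOVA on baseline log2 titre. Then:
- set results below 1:10 one fixed step below the cut-off;
- fix a rule for indeterminate results, for example counting them with those below the cut-off and, in a sensitivity analysis, at 1:10;
- report absolute and relative change descriptively only;
- describe the IVIG/PE arm without a formal comparison, in line with its exploratory reference role.

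The cost is a few sentences, with no new samples, visits or patients. It should be settled before week-16 titres are compared by arm, so that the choice of scale cannot look driven by the results.
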